**4) Introduction**

Admission to hospital with complicated severe acute malnutrition (SAM) in Africa commonly has a case fatality of 10-30%.[^1-3^](#_ENREF_1) Importantly, children are usually admitted to hospital because they are severely ill rather than for malnutrition alone. Mortality may be improved to some extent by adherence to WHO recommended management,[^1^](#_ENREF_1)^,^[^2^](#_ENREF_2) but the direct application of these guidelines to all contexts is controversial.[^4^](#_ENREF_4) The WHO guidelines were designed on the basis of historical data on nutrient requirements and medical treatments and almost none of the recommendations are supported by evidence from clinical trials.

For the treatment of complicated inpatient SAM, the guidelines consist of three distinct phases of treatment:[^5^](#_ENREF_5) phase 1 or stabilization phase where a low protein, liquid diet (F75) is introduced with a reduced energy intake (80-100 kcal/kg/day). Once a child has stabilised, there is a ‘transition phase’ consisting of either ready to use therapeutic foods (RUTF) with supplemental F75 or alternatively another milk formula known as F100. RUTF is a peanut based, energy dense supplement used to obtain catch-up growth. F100 is a liquid formula with a higher energy density and protein content than F75. The caloric intake is increased daily to a maximum of 130 kcal/kg/day. Finally, ‘Phase 3’ is the recovery phase during which the aim is to achieve catch-up growth with either RUTF or F100.

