Typically, the highest mortality rate is found in the early phases of treatment. Children who fail treatment early often have profuse diarrhoea, signs of circulatory insufficiency which is hard to treat. The most recent reports from Zambia and Kenya note a prevalence of diarrhoea of more than 60% amongst children with SAM and it is associated with increased mortality.[^6^](#_ENREF_6)^,^[^7^](#_ENREF_7) Currently at Kilifi County Hospital and Coast Provincial General Hospital, ~20% of children are given either a diluted or lactose-free milk feed during rehabilitation of SAM (unpublished data), although there are no specific guidelines for this. Diarrhoea may be caused by a viral or bacterial gastroenteritis, sepsis, or may be nutritionally induced (osmotic). There are no routinely available tests to distinguish osmotic from infective or other causes of diarrhoea in hospitals in sub-Saharan Africa. Rotavirus vaccine will be introduced in 2014 and its contribution to diarrhoea amongst children with SAM is unknown.

The proportion of energy derived from carbohydrates in F75 is high. The carbohydrates in F75 milk (as well as F100 and RUTF) consist of a mixture of maltodextrin, sucrose and lactose. Disaccharides such as maltose, lactose or sucrose are normally hydrolysed into monosaccharides by disaccharidases localized at the tip of small intestinal villi. The monosaccharides such as glucose and galactose can then be transported across the apical membrane through Na^+^ dependent glucose transporter, whilst fructose makes use of a facilitative fructose transporter. There is limited information on the intestinal function and intestinal carbohydrate absorption in malnourished children. However, data from Jamaica and South Africa suggest that there is impaired absorption of disaccharides (lactose and sucrose), regardless of the presence or suspicion of gastroenteritis.[^8^](#_ENREF_8)^,^[^9^](#_ENREF_9) Limited histological evidence has shown intestinal atrophy in children with SAM.[^10-12^](#_ENREF_10) These data are consistent with clinical signs of lactose malabsorption found in children with severe malnutrition.[^13^](#_ENREF_13) Recently, evidence of impaired absorption of monosaccharide glucose in children with SAM was reported in Malawi.[^14^](#_ENREF_14)

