***c) Sampling***

Children admitted with severe malnutrition, defined by anthropometry according to WHO guidelines, will be recruited at CPGH, Mombasa, Kilifi County Hospital and Queen Elizabeth Central Hospital (QECH), Blantyre, Malawi.

*Sample size calculation*

Based on clinical data from the actual sites, we have observed that around 50% of patients to have transitioned to the second phase of treatment by day 5. We aim for a 10% absolute increase in percentage transitioned at day 5 to 60%, which gives a hazard ratio of 1.35. Sample size for survival time was calculated using the *stpower* command in Stata version 12. Using α=0.05, 80% power, the number of patients required to demonstrate a hazard ratio of 1.35 is 381 per arm. We will aim at 420 per arm to allow for contingencies. It is anticipated that 400 children will be enrolled at CPGH, 120 at KCH and 320 at QECH. However, these figures will be adjusted in line with actual recruitment.

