Children will be examined daily whilst in hospital and clinical status recorded on a standardised proforma (appendix d). A blood sample and stool sample will be taken at day 3 to assess for metabolic effects of refeeding and carbohydrate malabsorption. If children deteriorate during the transition phase or phase 2 and are placed back on phase 1, they will receive the same F75 intervention diet as allocated during the initial treatment. The decision to discharge will be made by the usual clinical team rather than trial personnel. Food supplements and/or nutritional counselling and follow up in the nutritional clinic that are the current standard of care at each institution will also be done at discharge. No study follow up after discharge will be done.

[figure not shown]

*Outcome measures*

*Primary outcome:* the choice of primary outcome is based on the therapeutic purpose of F75, which is to achieve stabilisation and thereby allow a child to progress to feeds with higher protein and energy content to enable catch-up growth.

The primary outcome is stabilisation, defined as having reached the second (transition) phase of treatment. The criteria for stabilisation will be according to WHO guidelines:

Absence of any WHO danger or emergency signs: obstructed breathing, respiratory distress, cyanosis, shock (delayed capillary refill plus fast & weak pulse plus temperature gradient), severe anaemia (Hb<5g/dl), congestive cardiac failure, impaired consciousness, convulsions, severe dehydration, profuse watery diarrhoea, vomits everything, hypothermia.

*and*

If there is oedema at baseline, loss of oedema defined as improving from a severe +++ oedema (severe: generalized bilateral pitting oedema including feet, legs, arms and face) to ++ oedema (moderate: no upper arm or upper leg oedema and no facial oedema or from ++ oedema to + (mild: only feet/ankle oedema) or none;

*and*

Tolerating full prescribed volume of F75 feeds and observed to be completing the feeds.

For analysis, children who die before stabilisation will be classified as ‘not transitioned’.

*Pre-specified secondary outcomes*:

1. Number days with diarrhoea (3 or more loose stools within 24h);
2. Number days requiring rehydration fluids (ReSoMal or IV fluids);
3. Percentage change in weight between admission and day 5;
4. Changes in sodium, potassium, magnesium, calcium, phosphate and albumin between admission and day 3;
5. Faecal electrolytes, pH and fat at day 3;

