### (b) Data management/analysis

The trial will use the GCP-compliant Openclinica (<https://openclinica.com/> ) database system, which will be hosted at KWTRP in Kenya. Originally developed for small oncology trials, this system has become the leading open-source clinical data capture system for clinical trials. It allows secure remote data entry online from the sites, provides a real-time reporting system and flagging of inconsistencies and database changes for monitoring. We have used this system for several large clinical trials, which have been programed and maintained by the data manager who will be working on this trial. The trial will be register on clinicaltrials.gov along with pre-specified endpoints. Data cleaning and record verification will be completed and a written analysis plan agreed before the database is un-blinded.

Descriptive statistics on baseline characteristics of the participants in each arm will be provided. Bias will be determined by maintaining a screening log of all potentially eligible participants and those who were excluded or randomized into the two arms. This will be presented as a flow diagram in the final published report according to CONSORT statement guidelines.

The primary outcome will be assessed using a Kaplan-Meier analysis and Cox proportional hazards analysis comparing the rate of stabilisation between arms. Differences between arms in the number of days to stabilisation will be compared using a two tailed Mann-Whitney *U* test. Children who die prior to stabilisation will be included in the primary analysis as ‘not stabilised’. Secondary endpoints with binary outcomes (e.g. overall mortality) will be analysed using contingency tables and a chi squared test. Where adjustment for baseline parameters is required, relative risks will be calculated. For continuous variables and count data (e.g. days receiving rehydration fluids or days with diarrhoea), a suitable general linear model (e.g. linear regression, Poisson regression) will be used. For time to discharge, Kaplan-Meier and Cox proportional hazards analysis will be used. These analyses are conducted on the intention-to-treat principle and are considered the confirmatory analysis. We will conduct tests of heterogeneity of effect, and effect modification for both kwashiorkor and HIV infection, which are considered, *a priori,* to potentially alter the response to F75.

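### Deaths before stabilisation are to count as not stabilised, but Kaplan-Meier and Cox do not carry out that rule unless such children are given a time beyond death, and the protocol gives none.

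*Protocol*

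**What the plan says.** The rule for deaths appears twice. Under Outcome measures (section 8, d) the protocol writes: "For analysis, children who die before stabilisation will be classified as" not transitioned. In section 9 (b): "Children who die prior to stabilisation will be included in the primary analysis" as not stabilised.

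The method stands in the same paragraph of section 9 (b): "The primary outcome will be assessed using a Kaplan-Meier analysis and Cox proportional hazards analysis comparing the rate of stabilisation between arms". A second comparison follows: "Differences between arms in the number of days to stabilisation will be compared using a two tailed Mann-Whitney" U test.

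The sample size (section 8, c) starts from "around 50% of patients to have transitioned to the second phase of treatment by day 5", to be raised to 60%.

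On mortality, the Introduction says that inpatient treatment "commonly has a case fatality of 10-30" percent, and adds: "Typically, the highest mortality rate is found in the early phases of treatment".

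Follow-up runs until discharge. No section gives a day at which the primary outcome closes, or the time to be entered for a child who dies.

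**The concern.** The wording of the rule treats death before stabilisation as a failure of treatment. A survival routine does not know this. It receives a status and a time. Not stabilised supplies the status (no event), and the only time on record for a dead child is the day of death. The child is then censored on that day, and the estimate proceeds as if such children would have gone on to stabilise at the rate of those still at risk. That is not what the rule intends.

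Deaths are expected to be common and early, while children are still waiting for the primary event. Two results are at stake. The Kaplan-Meier curve no longer gives the percentage of children transitioned, which is the quantity the trial was sized on. The primary hazard ratio no longer responds to deaths before stabilisation, although the rule says they count. The Mann-Whitney test has a similar gap, because a dead child has no number of days to stabilisation and no rank is assigned.

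**Working it through.** **The plan's own figure.** 381 per arm reproduces with the Freedman log-rank formula, two-sided 0.05 and 80% power, with 0.50 and 0.60 entered as survival proportions:
- HR = ln 0.5 / ln 0.6 = 1.357.
- Events = (1.960 + 0.842)² × (2.357/0.357)² ≈ 7.85 × 43.6 ≈ 342.
- 342.3 / 0.45 / 2 = 380.3, so 381.

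The calculation rests on percentages of patients at day 5. The quantity it targets is therefore a proportion of all children, dead ones included.

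**Inputs for the check.** From the protocol: 50% of control children stabilised by day 5, and 420 per arm. Assumed: constant hazards s (stabilisation) and d (death), a share p of children dying before stabilisation, and a day-30 horizon. The 10-30% in the Introduction is case fatality for the whole admission, so p = 15% and p = 30% are illustrations.

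**Step 1: Kaplan-Meier with deaths censored.** With L = s + d and p = d/L, the true proportion stabilised by day 5 is (1 − p)(1 − e^(−5L)) = 0.50. The censored curve reads 1 − e^(−5s).
- p = 0.15: e^(−5L) = 1 − 0.50/0.85 = 0.412, L = 0.1775, s = 0.1508, d = 0.0266. The curve reads 1 − e^(−0.754) = 0.53.
- p = 0.30: e^(−5L) = 1 − 0.50/0.70 = 0.286, L = 0.2506, s = 0.1754. The curve reads 1 − e^(−0.877) = 0.58.

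**Step 2: only the death hazard doubles.** Take p = 0.15 in control, with s unchanged at 0.1508. In the modified arm d = 0.0532 and L = 0.2041.
- Deaths before stabilisation: 0.0532/0.2041 = 26%, against 15%.
- Truly stabilised by day 5: (0.1508/0.2041)(1 − e^(−1.020)) = 0.739 × 0.640 = 47%, against 50%.
- Cox with deaths censored: HR 1.00, because s is the same in both arms.
- Deaths kept as never stabilised: the ratio of ln(1 − proportion stabilised) is ln 0.527 / ln 0.500 = 0.92 at day 5. At day 30 it is ln 0.262 / ln 0.154 = 0.72. A Cox model run to day 30 averages over this and gives about 0.80 by simulation.

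**Step 3: deaths concentrated in slow stabilisers.** Assume 30% sicker children, with stabilisation hazard 0.06 against 0.20 per day and death hazard 0.08 against 0.01. The formula only doubles the death hazard, so deaths are 20% against 28%. By simulation the HR is about 1.07 with deaths censored and about 0.87 with deaths kept. A significant apparent benefit occurs in about 15% of trials when deaths are censored.

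**Step 4: a real benefit with the death hazard unchanged.** With s × 1.32, the HR is 1.32 censored and 1.23 kept. Power with 420 per arm is about 97% and 80%.

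**Step 5: Mann-Whitney.** Take s = 0.15 in both arms and a death hazard of 0.02 against 0.05 (deaths 12% against 25%), in 150 simulated trials. A test limited to stabilised children favours the modified formula in 43% of trials. With deaths ranked worst, it does so in none.

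**The case against.** The protocol nowhere says that deaths are censored at death. Included as not stabilised can also mean kept in the risk set to a common day, which is the handling recommended here. The protocol also promises a written analysis plan before unblinding, and that plan, which is not at hand, may settle the point. This stands as far as it goes: the rule and the method can be made compatible. But the protocol fixed both a rule and a method, and run in the ordinary way the method does not deliver the rule.

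A death-censored Cox model is not an error in itself. It estimates the stabilisation rate among children still alive and not yet stabilised, and the null hypothesis is worded as a rate. This also stands, and is why the cause-specific hazard ratio should be reported. It does not meet a rule that counts deaths as failures, and it does not rescue one minus Kaplan-Meier as a percentage of children.

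A reader might infer that a more lethal formula would readily win on the primary outcome. The documents do not support that. Extra deaths unrelated to readiness to stabilise give a hazard ratio of about 1, hiding the loss without creating a benefit. A case with the stabilisation hazard × 1.32 and the death hazard doubled does give a censored HR of 1.32, but the effect is built in: that arm is truly better at day 5 (56.6% against 50.0%) and worse only later. False benefit from deaths alone needs deaths concentrated in slow stabilisers, for which the protocol gives no figures.

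Mortality until discharge is a secondary outcome, and the DSMC reviews safety unblinded. Both could reveal harm, but neither corrects the primary estimate.

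**Conclusion.** The point holds as a gap between a stated rule and the method meant to apply it. It would go too far to call it an outright contradiction or a demonstrated false benefit, since censoring at death is the ordinary default and not the protocol's wording.

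Under that default, the day-5 percentage is overstated by about 3 points with 15% pre-stabilisation deaths and about 8 points with 30%. The hazard ratio reads 1.0 where keeping deaths gives about 0.8, and it can lean mildly towards the more lethal arm under assumed frailty. The two readings of the rule can therefore point in different directions on the same data.

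The sizes rest on assumed death shares, constant hazards, an assumed frailty split and a day-30 horizon, none of which the protocol gives. The kept hazard ratio itself moves with the horizon: where the stabilisation hazard rises 1.32-fold and the death hazard doubles, it is 1.21 at day 5, 1.07 at day 14 and 1.00 at day 30.

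**What to change.** In Outcome measures and in section 9 (b), or in the analysis plan, state the following:
- Children who die before stabilisation stay in the risk set as never stabilised to a pre-specified common day (or a subdistribution-hazard analysis is used).
- Cumulative incidence curves with death as a competing event replace one minus Kaplan-Meier, and the day-5 percentage of all randomised children is read from them.
- Cause-specific hazard ratios for stabilisation and for death are reported alongside.
- Deaths take the worst rank in the Mann-Whitney test.

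This costs a few sentences and no new data. The price is a somewhat smaller hazard ratio and lower power where the effect is real: about 80% against 97% with a true 1.32 and an unchanged death hazard. Because the result depends on the horizon, the day must be fixed before any unblinded comparison, including the interim analysis after 50% recruitment.

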**3) Summary**

Inpatient treatment for complicated severe acute malnutrition (SAM) continues to have a high mortality in Africa. This is partly because children are commonly brought for admission because they are seriously ill, rather than being brought to hospital because of malnutrition alone. Mortality rates are especially high where SAM is complicated by HIV or TB. The early phase of inpatient nutritional treatment for severe acute malnutrition is based on a low-protein milk known as F75, which is given to improve metabolic homeostasis prior to the re-feeding to achieve catch-up growth. F75 provides a high proportion of energy from carbohydrates, including sucrose, lactose and maltodextrin. However, malabsorption of different types of carbohydrates, but lactose in particular, is known to occur in SAM and may lead to osmotic diarrhoea. Diarrhoea is common in children with SAM and is associated with increased mortality. Furthermore, switching from a catabolic state to a high energy diet that consists of predominantly carbohydrates can lead to ‘re-feeding syndrome’ that may lead to severe electrolyte abnormalities and multiple organ dysfunction.

The aim of this trial is to determine whether reducing the carbohydrate content of F75, and removing lactose, improves the stabilisation of severely malnourished children. The trial will involve randomising children who are eligible to receive F75 milk to either the current formulation or a revised formulation. Both formulations will be given according to current recommendations regarding frequency of feeding and caloric value. Since the purpose of F75 is to stabilise the child metabolically and biochemically, the primary endpoint of the trial will be time to stabilisation (the end of the first phase of treatment for severe acute malnutrition). Blood and stool samples at admission and after three days will be used to determine the effects on carbohydrate and fat malabsorption and evidence of the re-feeding syndrome. Children will be followed up until discharge from hospital. The project has been planned in consultation with the World Health Organisation (WHO) and, if the revised formulation of F75 results in improved outcomes, will lead to a global change in recommendations for its formulation.

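### The protocol's analysis section labels the secondary-endpoint tests confirmatory along with the primary, although the trial has one null hypothesis and one comparison sized at 5%

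*Protocol*

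**What the plan says.** Section 9(b) of the protocol (Data management/analysis) goes through the planned tests in order. It starts with the primary outcome: "The primary outcome will be assessed using a Kaplan-Meier analysis and Cox proportional hazards analysis comparing the rate of stabilisation between arms", followed by a Mann-Whitney test on days to stabilisation. It then gives chi-squared tests for binary secondary endpoints, general linear models for continuous and count endpoints, and Kaplan-Meier with Cox for time to discharge. The next sentence reads: "These analyses are conducted on the intention-to-treat principle and are considered the confirmatory analysis". Tests of heterogeneity by kwashiorkor and HIV status come after it.

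Elsewhere the protocol is built around a single comparison. Section 6 has one null hypothesis, on the rate of stabilisation. Section 8(d) names one primary outcome. Section 8(c) contains the only significance level in the document: "Using α=0.05, 80% power, the number of patients required to demonstrate a hazard ratio of 1.35 is 381 per arm".

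The secondary list in section 8(d) has 13 items, some of which contain several measurements. Item 4, for example, is "Changes in sodium, potassium, magnesium, calcium, phosphate and albumin between admission and day 3", which is six analytes. Only item 11 is called exploratory.

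**The concern.** A confirmatory label says that a significant result may stand as proof of an effect at a known error rate. For the primary comparison that rate is 5%. For the whole set of tests covered by the sentence, this protocol gives no rate: there is no hierarchy, no split of alpha and no adjustment. The Haybittle-Peto criteria in section 8(d) deal with the single interim look, not with the number of endpoints.

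What is at stake is how the results may be described. If the primary comparison is null and one electrolyte or stool measurement gives p<0.05, the present wording would allow that result to be reported as confirmatory, in a trial that aims to influence treatment policy. The 5% error rate of the primary test is not affected.

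**Working it through.** **The plan's own figure.** Section 8(c) gives a control proportion of "around 50% of patients to have transitioned to the second phase of treatment by day 5" and a target: "We aim for a 10% absolute increase in percentage transitioned at day 5 to 60%, which gives a hazard ratio of 1.35". Freedman's log-rank formula, two-sided 0.05 and 80% power:

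- Events = (1.960 + 0.842)² × [(1+h)/(1−h)]², with (1.960 + 0.842)² = 7.849.
- Entering 50% and 60% as event-free proportions: h = ln 0.6 / ln 0.5 = 0.737 (inverse 1.357) and the mean event probability is 0.45. Events = 342.3, rounded up to 343; 343 / 0.45 / 2 = 381.1, which matches the stated 381 per arm.
- Entering them as proportions stabilised: h = ln 0.4 / ln 0.5 = 1.32, mean event probability 0.55, events 408.3, giving 371.2, so 372 per arm. The difference is under 3% and does not bear on this point.

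The calculation has one comparison and one alpha. The enrolment margin ("We will aim at 420 per arm to allow for contingencies") is for contingencies and is not linked to multiple endpoints.

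**How many tests the sentence covers.** Items 11 to 13 (item 11 labelled exploratory; microbiome; metabolite profiles) are left out, which keeps the count low.

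- One test per numbered item: items 1 to 9 plus the primary Cox test = 10; with item 10, 11.
- One test per measurement: items 1 to 3 give 3, item 4 gives 6, item 5 gives at least 3 (the number of faecal electrolytes is not stated), items 6 to 9 give 4. That is 3 + 6 + 3 + 4 = 16, or 17 with the primary Cox test. Adding the Mann-Whitney test, item 10 and a second faecal electrolyte gives up to 20.

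**Chance of at least one p<0.05 when the formula has no effect.** Assumption: each test at two-sided 0.05, a level the protocol does not state for secondary outcomes. For k independent tests the chance is 1 − 0.95^k. For results favouring the modified formula only, it is 1 − 0.975^k. The columns for correlation 0.5 use equicorrelated normal test statistics.

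| Tests k | Independent | Correlation 0.5 | Favourable only, independent | Favourable only, correlation 0.5 |
|---|---|---|---|---|
| 10 | 40% | 29% | 22% | 14% |
| 17 | 58% | 39% | 35% | 19% |
| 20 | 64% | 42% | 40% | 21% |

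For example, 1 − 0.95^10 = 0.401, 1 − 0.95^20 = 0.642 and 1 − 0.975^20 = 0.397. At weaker common correlation, 17 tests give 57% (0.1), 54% (0.2) and 49% (0.3). With 17 tests in related blocks (correlation 0.3 to 0.7 within blocks, 0.1 to 0.2 between) the chance is 51% to 53%.

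**After the change.** With only the primary Cox test confirmatory, the chance is 5%. With Bonferroni over 17 independent tests (0.05/17 = 0.00294 each) it is 1 − (1 − 0.00294)^17 = 4.9%.

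**The case against.** **The sentence may only set the main comparisons apart from the subgroup tests.** It is tied to intention to treat, uses the singular, and comes just before the kwashiorkor and HIV tests, so this reading is plausible. It still leaves the secondary outcomes on the confirmatory side. A contrast with a per-protocol analysis is less likely, since the protocol describes no such analysis.

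**Multiplicity across secondary outcomes is commonly left to the analysis plan.** This stands. Section 9(b) promises a written plan before unblinding, and that plan may set a procedure. A reader might infer that the trial has no error control across endpoints; the most that can be said is that this protocol states none. The label remains, because the protocol assigns that status itself.

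**No rule lets a single secondary establish efficacy.** This also stands. A reader might infer such a rule from the label together with the Summary, which says that, "if the revised formulation of F75 results in improved outcomes, will lead to a global change in recommendations for its formulation". But that is general language about policy impact, and the same paragraph names time to stabilisation as the primary endpoint. It is not a success criterion.

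**The size depends on choices the protocol does not make.** This is right too. A reader might infer that a false confirmatory result is more likely than not. That needs at least 14 independent tests (1 − 0.95^14 = 51.2%), or more if they are correlated. With one test per numbered item, or with correlation 0.5, the chance is below half. The two-sided figures also count results against the modified formula, and a favourable direction is not documented for every analyte.

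**Conclusion.** The point holds as a fault in the wording of section 9(b). Read literally, the section gives the secondary tests the same confirmatory status as the primary, which does not fit one null hypothesis, one primary outcome and one comparison sized at 0.05. Assuming two-sided 5% per test and no true effect, the chance of at least one false confirmatory result is about 40% to 64% for 10 to 20 independent tests and about 29% to 42% at a common correlation of 0.5. For results favouring the modified formula only, it is roughly 14% to 40%. Even the lowest of these is nearly three times 5%.

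These are ranges under stated assumptions, not figures from the protocol. Nothing here shows that the primary analysis is invalid or that the analysis plan lacks a procedure.

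**What to change.** Reword the sentence in section 9(b) before unblinding so that it says three things:

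- All analyses follow intention to treat.
- Only the comparison of time to stabilisation is confirmatory, at two-sided 0.05. The Cox analysis is the natural choice because the sample size rests on a hazard ratio; the Mann-Whitney test then becomes supportive.
- Secondary outcomes are supportive and are reported with effect sizes and 95% confidence intervals.

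If the investigators want any secondary outcome to stay confirmatory, they should name it and state the multiplicity procedure. The analysis plan should use the same wording. The Summary sentence on improved outcomes need not change.

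The cost is one reworded sentence, with no change to data collection or sample size. The real downside is that a positive secondary result could no longer be called confirmatory, and the Mann-Whitney result would not carry the primary conclusion.
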